### Concealment mechanism {16b}

Each number and the group to which a number is allocated will be concealed in sequentially numbered, opaque, sealed, and stapled envelopes. Only investigators can open the envelope, at the moment of intervention, to check the group to which the number is allocated, and perform the interventions according to the instructions of this study.

### Implementation {16c}

The randomization list is implemented in the software by the study statistician ([name]). Access to the randomization list is limited to the study investigators.

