#### Exclusion criteria

Patients may not participate in the study if they are as follows: (1) teeth with extensive coronary destruction that makes direct restoration with composite resin unfeasible, (2) calcified teeth, (3) teeth with incomplete root formation, (4) teeth with persistent exudation, (5) teeth with anatomical complexities that prevent endodontic treatment in a single visit, (6) teeth recommended for endodontic retreatment, (7) teeth with advanced periodontal pocket, and (8) teeth in which foraminal patency is not obtained.

Patients who present a profile that fits to that described in the inclusion and exclusion criteria will then be referred for evaluation by other examiners ([name], [name], and [name], experts in Endodontics for more than 15 years), for confirmation of diagnosis and treatment planning, if necessary. Patients who do not fit the required profile will be forwarded to the health unit of origin. All the steps of interviews and clinical examination necessary to complete the diagnosis will be carried out by the examiners who will perform the treatment.

Patients with systemic diseases (diabetes, transplants, heart disease, liver failure, and kidney failure) and immunodepressed patients are prohibited during the trial as these conditions can affect the oral functions.

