### Outcomes {12}

All the steps of clinical examination will be carried out by the two examiners responsible for the study. Imaging evaluation will be done by other 2 specialists in Endodontics and 1 radiologist. All are with at least 15 years of experience.

Assessments will also be carried out at 6 (IOPAR), 12 (IOPAR), and 24 (CBCT) months for analysis of the tissue repair process. The therapeutic effect evaluation criteria are the following: (1) success: after RCT, the tooth should be asymptomatic, without fistula, without pain on percussion and palpation tests, without edema and in normal chewing function, radiographically in the process of periapical lesion regression from the first assessment (time point) at 06 months, and fully repaired after 2 years with confirmation through CBCT; and (2) failure: after RCT, the tooth is symptomatic, with symptoms of apical infection such as pain and fistula. The radiographic examination demonstrates the absence of decreased apical lesion or an enlarged apical lesion [22, 23].

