## Assignment of interventions: blinding

### Who will be blinded {17a}

As a double-blinded trial, the patients and outcome evaluators will be blinded to the group assignment until the completion of the study. As dentists cannot be blinded to treatment allocation due to the notable differences in the treatment methods, they will not be allowed to discuss the type of intervention with either patients or outcome evaluators.

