## Data collection and management

### Plans for assessment and collection of outcomes {18a}

Data associated with this study will be collected in the standardized case report forms (CRF) for the outcome analysis, and a specific supervisor will be responsible for reviewing the integrity, accuracy, and consistency of the data. To ensure the accuracy of data entry, three investigators (two endodontists and 1 radiologist) will be responsible for entering the data independently and data query forms (DQF) will be resolved by tracing the source data.

A questionnaire to score the patient postoperative pain levels will be administered by two investigators in periods of 24, 48, and 72 h and 7 days after the completion of a root canal treatment. Questionnaires of patient satisfaction rate with regard to the treatment and the patient preference in relation to the frequency of clinical visits will also be performed. The secondary outcomes will be obtained from self-administered questionnaires completed immediately after the completion of a root canal. All the data will be registered in document clouds (in a specific Microsoft 365 OneDrive institutional account files), and only authorized personnel will have access. Data monitoring will be independent from the investigators and competing interests.

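### The protocol's list-access rule defeats its envelope concealment as written, and the double-blind label does not hold for group 1 against groups 2 and 3

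*Protocol article*

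**What the plan says.** **Concealment.** Under Concealment mechanism {16b}, each number and its group "will be concealed in sequentially numbered, opaque, sealed, and stapled envelopes". The same section continues: "Only investigators can open the envelope, at the moment of intervention, to check the group to which the number is allocated, and perform the interventions". Implementation {16c} has the statistician implement the list and adds: "Access to the randomization list is limited to the study investigators". Procedure for unblinding if needed {17b} expects no unblinding and opens the allocations to the principal investigator or the data manager only if it is required.

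**Blinding.** The Abstract (Methods), Objectives {7} and Trial design {8} call the trial double-blinded. Who will be blinded {17a} states that "the patients and outcome evaluators will be blinded to the group assignment until the completion of the study", and accepts that the dentists cannot be blinded.

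**Who examines.** Outcomes {12} says: "All the steps of clinical examination will be carried out by the two examiners responsible for the study". Imaging goes to other readers, two endodontists and a radiologist. Under Exclusion criteria, the interviews and examinations needed for the diagnosis "will be carried out by the examiners who will perform the treatment". Study setting {9} places the work in the private offices of two co-investigators, and Recruitment {15} has those offices identify and refer participants.

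**The concern.** Envelopes protect against selection only if nobody who decides on entry can learn the next assignment another way. If an enrolling dentist can read the list, the decision to admit a particular tooth, or when to admit it, can depend on the arm it would receive. Several exclusions leave room for this because they rest on the operator's judgement: persistent exudation, calcification, failure to obtain patency, and anatomy that rules out single-visit treatment. The last bears directly on one arm.

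Blinding matters in a similar way. Success in Outcomes {12} is a composite of imaging and clinical signs (symptoms, fistula, percussion and palpation pain, edema, chewing function). Pain and satisfaction are reported by the patient. An examiner or patient who knows the arm can let expectation shape these answers. The trial report would nevertheless describe both protections as in place.

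**Working it through.** There is no figure to reproduce. The check follows each role through the Protocol article.

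1. **Who may see the list.** Concealment mechanism {16b}: nobody before the moment of intervention. Implementation {16c}: the study investigators, with no exception for those who enrol, treat or assess. Procedure for unblinding {17b}: the principal investigator or data manager, and only if required. These three rules cannot all hold. If {16c} holds, the other two restrict nothing.

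2. **Are the list-holders the people who enrol and treat?** Section {16b} uses investigators for those who open the envelopes and perform the interventions. Recruitment {15} runs through the two co-investigators' offices. Exclusion criteria gives the diagnostic examination to those who will treat. Read together, the group allowed to see the list includes those who recruit, judge eligibility and treat. Concealment is therefore defeated as written.

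3. **Can patients be blinded?** Under Trial design {8}, group 1 is finished in one visit, while groups 2 and 3 return after 7 days.
   - Group 1 v group 2, and group 1 v group 3: the number of visits shows the patient which side of the comparison they are on. Masking is impossible.
   - Group 2 v group 3: same number of visits and same interval, and {17a} forbids dentists to discuss the intervention. Masking is feasible, although the temporary filling differs (glass ionomer v composite resin) and the protocol does not say whether a patient would notice.

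4. **Is the clinical part of success judged blind?** Outcomes {12} gives all clinical examination to two examiners responsible for the study. Study setting {9} describes two co-investigators' offices, and Exclusion criteria says the diagnostic examiners treat. The natural reading is that these are the same two people, whom {17a} describes as unblinded. This is an inference across sections: the sentence under Exclusion criteria concerns diagnosis at entry, and no sentence names the follow-up examiners as the operators.

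5. **Are the image readers blinded?** Outcomes {12} assigns them separately from the clinical examiners, so blinded reading is possible. Nothing secures it: if they count as study investigators, {16c} gives them the list, and the sections cited here provide neither for coded images nor for keeping treatment records from the readers.

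**The case against.** The strongest reply is that the term study investigators is not defined in {16c}. It may mean a small coordinating group, and {17b} suggests access was meant to be narrow. Exclusion criteria also sends candidates to other experienced examiners to confirm the diagnosis if necessary, and the exclusions already remove many difficult teeth, which leaves less room for steering. All of this is fair, and it means the text does not prove that any enrolling dentist has seen the list. It does not remove the contradiction, because {16c} sets no such limit and {16b} uses the same word for those who treat.

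A reader might go further than the text in three ways.

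- *That concealment and blinding are wholly absent.* This is not supported. Imaging, on which the PAI primary outcome rests, is read by people other than the clinical examiners, and groups 2 and 3 can be masked from each other.
- *That the image readers enter the case report data and so learn the arm.* Plans for assessment and collection of outcomes {18a} says "three investigators (two endodontists and 1 radiologist) will be responsible for entering the data independently". That matches the make-up of the reading panel, but the document does not say they are the same people or that the forms show the arm.
- *That the bias can be put in percentage points.* The documents give no success rates by difficulty of tooth and no proportion of difficult teeth, so any such number would be assumed.

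**Conclusion.** The point holds in this form. The rules on access to allocation contradict each other, and the list-access rule defeats concealment as written. The double-blind claim is wrong for patients in the two comparisons that involve group 1, out of three pairwise comparisons. It is contradicted for the clinical part of success if, as the sections together suggest, the two examiners are the treating dentists. For image reading it is achievable but not secured.

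The conclusion on concealment assumes that the word investigators means the same in {16b} and {16c}. The conclusion on patients needs no assumption beyond the visit schedule. The direction and size of any bias cannot be derived from the documents. The defect still needs correcting because it concerns safeguards that the report would claim, and because clinical signs, pain and satisfaction are all open to expectation.

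**What to change.** - **Implementation {16c}.** State that only the study statistician, or another person who does not enrol, treat or assess, holds the list. Reconcile this with {17b}: when unblinding is required, the principal investigator or data manager obtains the single allocation concerned from the list-holder, and the release is recorded.
- **Access to date.** Trial status says recruiting began in August 2021, so a change of wording cannot protect allocations already made. Document who has had access. If anyone who enrols, treats or assesses has seen the list, regenerate the unused part of the sequence and disclose this in the report.
- **Image reading.** State in Outcomes {12} or {18a} that readers receive coded images and have no access to allocation or treatment records.
- **Label.** In the Abstract, Objectives {7}, Trial design {8} and {17a}, replace double-blinded by image-assessor-blinded, and note that patients can be masked only between groups 2 and 3. Interpret pain, satisfaction and clinical signs as unblinded in comparisons with group 1.
- **Follow-up examination.** Reconcile Outcomes {12} with {17a}: either name a non-treating, masked examiner or say that this component is unblinded.
- **Reporting.** Show imaging-only repair (PAI/CBCT) beside the composite, so that the component that can be blinded is visible alone.

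Most of this costs only protocol wording, an access change and the coding of images. A separate clinical examiner would add staff time at two sites, and regenerating the sequence would need new envelopes. The trial also gives up the double-blind label.

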## Assignment of interventions: blinding

### Who will be blinded {17a}

As a double-blinded trial, the patients and outcome evaluators will be blinded to the group assignment until the completion of the study. As dentists cannot be blinded to treatment allocation due to the notable differences in the treatment methods, they will not be allowed to discuss the type of intervention with either patients or outcome evaluators.

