### Trial design {8}

This is a randomized, double-blinded, paralell group, non-inferiority controlled trial.

The trial protocol conforms with the Consolidated Standards of Reporting Trials (CONSORT) Statement. The trial design and protocol adhere to the Standard Protocol Items of the Recommendations for Interventional Trials (SPIRIT) criteria.

The study aims to compare the efficacy of endodontic treatments conducted in a single visit using ultrasonic irrigant activation and in two visits also using ultrasonic irrigant activation, with and without the use of calcium hydroxide dressing, in lower molar teeth with asymptomatic apical periodontitis (Fig. 1, “Study flowchart”).

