## Interventions

### Explanation for the choice of comparators {6b}

Traditionally, root canal treatment in teeth with apical periodontitis is performed in multiple visits, with the use of intracanal dressing between visits, aiming to reduce microorganisms and their by-products from the root canal system prior to filling. However, this type of conventional endodontic treatment has as a disadvantage the inconvenience of requiring patient return (in multiple sessions) for medication changes, until the root canal filling is possible. In the comparison group, the root canal treatment will be performed in a single session, which represents a more objective form of treatment, with the convenience of only one appointment for the patient and a lower operating cost for the professional.

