##### Group 1—root canal treatment in a single visit (RCT-SV)

(1) The root canals will be filled in the first visit. In this group, a #30/.05 gutta-percha cone and epoxy resin-based sealer with the continuous heat wave technique and a final restoration with Z250 composite resin (3M ESPE, St. Paul, USA) will be used.

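### The trial is called double-blinded with patients blinded to group, but patients know whether they had one visit or two, so two of the three pairwise contrasts are open-label to the patient

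*Protocol article*

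**What the plan says.** Trial design {8} states: "This is a randomized, double-blinded, paralell group, non-inferiority controlled trial". The abstract and Objectives {7} use the same label. Who will be blinded {17a} spells it out: "the patients and outcome evaluators will be blinded to the group assignment until the completion of the study". It names only one party that cannot be blinded: "As dentists cannot be blinded to treatment allocation due to the notable differences in the treatment methods". Its one safeguard concerns what dentists say: "they will not be allowed to discuss the type of intervention with either patients or outcome evaluators".

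The interventions differ in number of appointments. For group 1, "The root canals will be filled in the first visit", and the final restoration is placed then. Under Second clinical appointment, groups 2 and 3 come back after 7 days for new anaesthesia, removal of the temporary restoration, repeat preparation, filling and final restoration.

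Pain, satisfaction and visit preference are all reported by patients. On collection, Plans for assessment and collection of outcomes {18a} says two things. First: "A questionnaire to score the patient postoperative pain levels will be administered by two investigators", at 24, 48 and 72 hours and 7 days after completion. Then: "The secondary outcomes will be obtained from self-administered questionnaires completed immediately after the completion of a root canal".

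**The concern.** A rule against discussing the intervention cannot hide how many appointments a patient attended. Someone in group 1 knows that treatment ended in one visit, and someone in group 2 or 3 knows that it took two. The protocol thus claims patient blinding that the described interventions rule out for any comparison involving group 1.

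The group 1 comparisons are central to the trial, because they answer the single-visit versus two-visit question. If their pain results are reported as double-blind, readers will take a difference as an effect of treatment when part of it could come from expectation. They will likewise take a null result as free of expectation effects that could have masked a difference. The definition of success under Outcomes {12} also requires an asymptomatic tooth with no pain on percussion or palpation, so patient responses enter the same two contrasts there.

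**Working it through.** **Step 1: visits per group.** From the group descriptions and Second clinical appointment: group 1 = 1, group 2 = 2, group 3 = 2. No sham visit for group 1 appears anywhere in the article.

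**Step 2: the three pairwise contrasts.**

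| Contrast | Visits | Can the patient be blinded? |
|---|---|---|
| Group 1 vs group 2 | 1 vs 2 | No |
| Group 1 vs group 3 | 1 vs 2 | No |
| Group 2 vs group 3 | 2 vs 2, same 7-day interval | In principle |

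Two of three are open-label to the patient. The third is blindable only in principle, because the temporary restoration is glass ionomer cement in group 2 and composite resin in group 3.

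**Step 3: which outcomes are reached.**

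- *Pain*: self-rated 0 to 4, at 24 hours to 7 days after completion, when the number of visits is known. Compared across groups by Kruskal-Wallis. Directly exposed.
- *Satisfaction*: self-rated 1 to 5 after treatment, also compared by Kruskal-Wallis. Exposed, but convenience is partly a real feature of the treatment.
- *Preference*: the question is about number of visits and is put in hypothetical terms, so patient blinding means little here.
- *Success, symptom component*: exposed, because it depends on symptoms and on responses to percussion and palpation.
- *PAI and CBCT reading*: done by two other endodontists and a radiologist (Outcomes {12}). Not affected by what the patient knows.

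**Step 4: how large could the effect on pain be?** The protocol gives no pain distribution and no misreporting rate, so any figure is an illustration. Setup: five pain categories, three arms, no true difference, Kruskal-Wallis at 5%. A fraction f of group 1 patients with pain report one category lower. The main settings used 6,000 simulated trials each. Arm sizes are 210/3 = 70 teeth and 150/3 = 50 patients, and scores are treated as independent.

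| Assumed pain distribution, categories 0 to 4 | Per arm | f = 0 | f = 0.05 | f = 0.10 | f = 0.20 | f = 0.40 |
|---|---|---|---|---|---|---|
| 50/30/15/4/1% | 70 | about 5% | 5.4% | 6.0% | about 10% | 29 to 30% |
| 50/30/15/4/1% | 50 | about 5% | – | – | about 9% | 21 to 22% |
| 80/14/4/1.5/0.5% | 70 | – | – | – | 6.4% | 13.7% |

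The rejection rate therefore lies anywhere from about 5% to 30%. The downward shift is itself assumed; reports could equally shift upward.

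**Step 5: the two statements on collection.** One has investigators administering the pain questionnaire at 24 hours to 7 days. The other has the secondary outcomes self-administered immediately after completion. They differ in mode and timing, and a form filled in immediately after completion cannot record pain a day or a week later.

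**The case against.** The strongest reply is about reach. The primary measure is the PAI, read by specialists separate from the two clinical examiners, and a patient's knowledge of visit number cannot move a radiographic score. That stands. A reader might infer that the primary result as a whole is unblinded; the documents do not support this beyond the symptom component of success.

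A reader might also infer that all three patient-reported outcomes are equally biased. They are not. Preference is about visit number itself. For satisfaction, Explanation for the choice of comparators {6b} offers treatment "with the convenience of only one appointment for the patient" as a genuine advantage, so some of any difference is effect rather than bias. The expectation argument is clean mainly for pain.

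The upper rejection rates should not be read as what this trial will suffer. They come from one assumed distribution, larger misreporting fractions and an assumed direction. At f of 0.10 or less the rate hardly moves, and the Discussion mentions fear of pain after single-visit treatment, which could raise group 1 reports.

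It is tempting to conclude that the unblinded treating dentists collect the pain scores. The two investigators are not identified there, and administering a form may only mean handing it out. The inconsistency in mode and timing remains.

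Finally, open-label patient-reported outcomes may legitimately be tested, so nothing here requires the group 1 contrasts to be reduced to description. None of these replies restores the claim that patients are blinded to group.

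**Conclusion.** The point holds as a misstatement of the design. Patients cannot be blinded to one visit versus two, so two of the three pairwise contrasts are open-label to the patient. This follows from the described interventions and needs no assumption beyond the absence of a sham visit. It affects self-reported pain most, satisfaction less, and the symptom component of success; blinded image reading is untouched. Group 2 versus group 3 should not be called patient-blinded outright, since the different temporary restorations leave it blindable only in principle. The possible bias in pain cannot be sized from the document: the range of about 5% to 30% rejection under no true effect is conditional on the assumptions shown, and the direction is unknown. The correction is worth making because it changes how the single-visit versus two-visit results on pain and satisfaction may be read.

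**What to change.** - In the abstract, Objectives {7}, Trial design {8} and Who will be blinded {17a}, replace the double-blinded label with: *blinded image readers; patients not blinded to number of visits*.
- In {17a}, state that only group 2 versus group 3 can in principle be patient-blinded, and note the different temporary restorations.
- In Secondary outcome analysis, state that pain and satisfaction contrasts with group 1 may be tested but are to be interpreted as open-label. Add the same caution for the symptom component of success.
- In {18a}, reconcile the two statements on collection: patients complete the pain form themselves at 24, 48 and 72 hours and 7 days, and the form completed immediately after treatment is limited to the outcomes it can capture.

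The cost is protocol wording and self-completed pain forms at four time points. No extra patients or treatment visits are needed and no treatment changes. The downside is a less favourable blinding claim and more cautious conclusions on pain and satisfaction.
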